Content. The breastfeeding messages will be developed following the COM-B system (capability, opportunity, motivation, and behaviour) and Social Cognitive Theory as the underlying theoretical frameworks [118]. The mother’s capability refers to knowledge about the benefits of breastfeeding, and skills in breastfeeding. Opportunity includes support provided by health professionals or family members on breastfeeding. Motivation refers to a desire to perform the behaviour, forming plans and goals of early initiation of breastfeeding and exclusive breastfeeding [96]. Because of the importance of social norms, notifications will be targeted based on caregivers’ attitudes toward breastfeeding [119,120]. Notifications and relevant records on breastfeeding will be released to the intervention group to empower mothers through information and motivation:establish beliefs on the benefits of exclusive breastfeeding until 6 months;enhance the perception of sufficient breastmilk, for both vaginal delivery and caesarean section mothers;plan/commit to breastfeeding exclusively from birth;benefits and feasibility of early initiation of breastfeeding;overcome difficulties of breastfeeding; able to breastfeed without pain/problems;encourage mothers to seek advice and maintain communication with health professionals;involve husbands and grandmothers in preparation for exclusive breastfeeding;ask friends and relatives not to bring gifts of infant formula to the hospital or to the home.

Breastfeeding messages will not be released to the control group. The control group will receive notifications and library information on maternal and child health care only (see Figure 1). Relevant health education materials and guidelines from the Vietnam Ministry of Health, the National Institute of Nutrition, World Health Organization, infant feeding guidelines for the Asia Pacific Region, and the Australian government on infant feeding will be adapted to develop the library contents [25,121].

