### 2.4. Outcomes

To evaluate the effectiveness of the mobile app, data will be collected five times from all participants: At enrolment, before discharge from hospital, 1 month, 4 months, and 6 months postpartum. The first two data collections will be conducted by face–to–face interviews and the three follow up surveys will be performed through telephone conversations. Definitions of breastfeeding from the World Health Organization (2008) will be adopted for the evaluation of the outcomes [5], based on both recall of the previous day and recall since birth methods [5,122,123]:early initiation of breastfeeding: Proportion of infants at the first month of age who were put to the breast within one hour of birth;exclusive breastfeeding: Proportion of infants at 1, 4, 6 months of age who were fed by breast milk only during the previous day, and from birth;predominant breastfeeding: Proportion of infants at 1, 4, 6 months of age who received breast milk as the predominant source of nourishment during the previous day, and from birth;any breastfeeding: Proportion of infants at 1, 4, 6 months of age who were ever breastfed;duration of exclusive breastfeeding: The age in weeks when infants received only breast milk from birth;introduction of complementary and solid foods: Proportion of infants at 1, 4, 6 months of age who received solid, semi-solid, or soft foods.

Confounding variables will be identified from an extensive literature review, including: (1) Socio-demographic characteristics such as age, marital status, education level, occupation, household income, parity, smartphone usage experience; (2) obstetric and birth outcomes: Complications during and after pregnancy, mode of delivery, length of hospital stay, infant gender, birth weight and length; (3) breastfeeding attitude and intention on breastfeeding. Such information will be collected prospectively from the baseline and follow up surveys.

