### 3.5. Analytical Methods 

Data will be collected and managed using REDCap [131] and exported to Statistical Package for the Social Sciences, SPSS. Survival analysis will be used to compare the exclusive breastfeeding duration between the intervention and control groups. The Kaplan–Meier curves will be used for estimating the median exclusive breastfeeding times, and the log-rank test will be used to assess the differences between groups. Multivariable logistic regression and repeated measures mixed modelling will be applied to determine the effect of the intervention on exclusive breastfeeding prevalence at different time-points, accounting for delivery method, and other confounding factors. Intention-to-treat analysis will be performed in the presence of missing data to accommodate the expected attrition and withdrawal of participants from the study. All statistical analyses will be performed in SPSS (IBM Corp. Released 2017. IBM SPSS Statistics for Windows, Version 25.0. Armonk, NY, USA: IBM Corp).

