### Strengths and Limitations

This trial hypothesizes that there will be higher rates and longer duration of exclusive breastfeeding for up to 6 months after childbirth in the intervention group compared with its control counterpart. The study, to our knowledge, will be the first mobile app-based intervention to support breastfeeding in Vietnam. A blinded randomised control trial that can provide the most rigorous evidence of intervention effectiveness. The intervention content will be developed by experts in the field, and an app will be designed for two common mobile operating systems (iOS and Android). Data collection and management will be undertaken in a secured environment through REDcap so that data quality and protection can be ensured. The study will fill an important gap by developing a novel mHealth intervention addressing suboptimal breastfeeding in LMICs.

However, the study has some limitations. The intervention and control group may differ in terms of socio-demographic characteristics, potentially limiting comparison between the two groups on breastfeeding outcomes. Nonetheless, a statistical analysis plan will be developed, including adjustment for baseline covariates [139,140,141]. In fact, the CONSORT statement recommended against performing significance testing of baseline differences in randomised controlled trials [142]. Moreover, a stratified permuted-block randomisation will be undertaken with consideration of three key factors (i.e., maternal age, education and parity) associated with breastfeeding behaviours, perception and practices. Loss to follow-up is also a matter of concern because it may bias the results [143], particularly if missing data is associated with breastfeeding. To cope with this potential problem, we will adopt different strategies to maintain a high level of participant retention such as building positive rapport between participants and the study team, sending reminders, providing incentives, etc. [144,145,146]. In addition, appropriate methods will be applied to handle missing data, including inverse probability weighting, likelihood-based methods, and multiple imputation [147,148]. Another possibility is no or low usage of the mobile app under the study, but we will send reminders to encourage participants and conduct intention-to-treat analysis accordingly.

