## 5. Conclusions

Breastfeeding has many advantages for mothers and infants in the short term and for lifetime health. The coverage in Vietnam of mobile phones is now above 90% making it eminently feasible to use smart phones for promoting breastfeeding. The app will be developed to promote early initiation of breastfeeding and exclusive breastfeeding for the first six months of life. In particular, the app will seek to overcome the low rate of breastfeeding following caesarean section. 

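### The models for exclusive breastfeeding prevalence adjust for delivery method and draw on a confounder list that mixes pre- and post-randomisation variables; the main model should use pre-randomisation covariates only

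*Protocol article*

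**What the plan says.** Section 3.5 names multivariable logistic regression and repeated-measures mixed modelling for the effect on exclusive breastfeeding prevalence at the different time points, "accounting for delivery method, and other confounding factors". These are the only models stated for prevalence. Duration of exclusive breastfeeding is compared separately by Kaplan–Meier curves and a log-rank test, with no adjustment mentioned.

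Section 2.4 lists the confounding variables in three groups. The first is socio-demographic. The second is obstetric and birth outcomes: "Complications during and after pregnancy, mode of delivery, length of hospital stay, infant gender, birth weight and length". The third is "breastfeeding attitude and intention on breastfeeding". On timing it says only: "Such information will be collected prospectively from the baseline and follow up surveys". No variable is assigned to a particular survey.

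Section 2.2 recruits women at 24–36 weeks of gestation, and section 3.3 randomises each woman once her baseline interview is complete. Section 2.3 gives the app's targets, which include motivation, beliefs and the aim that mothers "plan/commit to breastfeeding exclusively from birth". The Strengths and Limitations section states that "a statistical analysis plan will be developed, including adjustment for baseline covariates".

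**The concern.** Randomisation removes systematic confounding of the comparison between arms. A variable that arises after allocation cannot be a common cause of allocation and outcome. It may be a consequence of allocation, a consequence of the outcome, or unrelated to allocation. Adjusting for a consequence of allocation that lies on the path to breastfeeding leaves only the part of the effect that bypasses it. If that variable also shares an unmeasured cause with the outcome, adjustment can create an apparent effect, or hide a real one, even in a large trial.

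The trial was sized on 6-month exclusive breastfeeding prevalence (section 2.5), and the only models stated for prevalence are the adjusted ones. If the adjustment set contains variables changed by the app, the reported effect is no longer the total effect that the sample size assumed. The unadjusted log-rank test does not cover this, because it addresses duration.

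**Working it through.** **1. Timing of each listed variable (sections 2.2, 2.4 and 3.3).** Randomisation takes place in pregnancy, after the baseline interview.

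| Listed variable | Relation to randomisation | Does the document say the app or breastfeeding changes it? |
|---|---|---|
| Age, marital status, education, occupation, income, parity, smartphone experience | Before | No |
| Complications during pregnancy | Before or after, not specified | No |
| Complications after pregnancy | After | Yes, in part: section 1.1 says breastfeeding reduces post-partum haemorrhage and infection |
| Mode of delivery | After | No |
| Length of stay, birth weight and length | After | No |
| Infant gender | Fixed before, recorded later | No |
| Attitude and intention | Not specified | Section 2.3 makes motivation, plans and commitment targets of the app |

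Two entries carry the main risk. By the document's own account, postpartum complications can be a consequence of breastfeeding. Attitude and intention are proper covariates if measured at enrolment, and mediators if measured at follow-up.

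**2. The plan's own figure.** Inputs from section 2.5: 12.6% against 20%, 80% power, 5% significance (taken as two-sided). With pooled variance and no continuity correction:

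n per group = [1.960·√(2·p̄·(1−p̄)) + 0.842·√(p₁(1−p₁)+p₂(1−p₂))]² / (p₂−p₁)²

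with p̄ = 0.163. The terms are 1.960·√0.2729 = 1.024 and 0.842·√0.2701 = 0.437. Their sum squared is 2.135, and 2.135/0.074² = 389.9, so 390 per group and 780 in total. The stated figure reproduces, and power at 390 per group is 80.0%.

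**3. What adjustment could do.** All path strengths below are assumptions; the document gives none. The simulation used 400,000 records, a binary covariate and a control rate near 12.6%, with power scaled to 390 per arm.

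| Assumed situation | OR unadjusted | OR adjusted | Power unadjusted | Power adjusted |
|---|---|---|---|---|
| Covariate predicts outcome (log-OR −0.7) but the app does not move it | 1.71 | 1.73 | 77% | 78% |
| App moves covariate (log-OR 0.8); covariate predicts outcome (log-OR 1.0) | 1.71 | 1.46 | 78% | 46% |
| No true effect; app moves covariate (log-OR 0.8); an unmeasured cause affects covariate and outcome (log-OR 1.0 each) | 1.00 | 0.89 | – | – |

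The first row is the relevant case for delivery mode if the app leaves it unchanged: there is no attenuation. The second row shows attenuation through a mediator, and the third shows bias with no true effect.

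**4. The same point on the risk scale.** Suppose a share m of the 7.4-point difference passes through an adjusted variable. The remaining intervention rate is 0.126 + 0.074·(1−m), and power at 390 per arm is:

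- m = 0: 20.0%, power 80%
- m = 0.25: 18.15%, power 57.5%
- m = 0.50: 16.3%, power 31%
- m = 0.75: 14.45%, power 11%

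The document does not support any value of m. The list shows only that the result depends on whether, and how far, the app moves the covariates adjusted for.

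**The case against.** The strongest reply has four parts.

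*Attitude and intention may be enrolment measurements.* The timing sentence in section 2.4 covers the whole list, and its natural reading is that each item is recorded at the survey where it arises. This stands. A reader might infer that follow-up attitude or intention enters the model, but no section says so. The text only fails to rule it out.

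*The app is not said to change delivery mode, length of stay or birth weight.* Section 2.3 treats vaginal and caesarean delivery as given circumstances. This also stands, so one cannot say that adjusting for delivery method, the only covariate section 3.5 names, removes the effect. It does not justify calling such a variable a confounder, and it does not cover postpartum complications.

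*The baseline-covariate statement need not exclude other covariates, and section 2.4 does not say that every listed variable enters one model.* This is fair. The passages fit poorly together without flatly contradicting each other. For the same reason a charge of overfitting is not supported: the number of parameters is nowhere stated.

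*Subgroup analyses are commonly left to the statistical analysis plan.* Given the aim in section 5 ("In particular, the app will seek to overcome the low rate of breastfeeding following caesarean section"), a reader might object that delivery method appears only as an adjuster. The absence of a caesarean subgroup analysis from a condensed article is not a fault.

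What survives is that section 3.5 fixes adjustment for a variable known only after randomisation, and refers to further confounders whose list mixes pre- and post-randomisation items.

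**Conclusion.** The concern holds in a limited form. The stated adjustment rule is wrong in principle for a randomised comparison, and it sits badly with the document's own reference to baseline covariates. It may attenuate or bias the total effect if the model takes in postpartum complications, or attitude and intention measured at follow-up. Whether it would do so, and by how much, cannot be derived from the document; the odds ratios and power figures above illustrate assumed paths and do not predict this trial's result. Adjusting for delivery mode alone may do little harm, provided the app does not change it. The stronger reading, that the plan as written would hide an effective intervention, is not supported.

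**What to change.** Reconcile sections 2.4 and 3.5 with the Strengths and Limitations section, before unblinding:

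- Limit the main effect model for prevalence to pre-randomisation covariates: the stratification factors age, education and parity, plus attitude and intention measured at enrolment.
- State in section 2.4 the survey at which each listed variable is measured, in particular attitude, intention and complications.
- Use delivery mode, post-delivery complications, length of stay, birth weight and length, and any follow-up attitude or intention only for descriptive, exploratory subgroup or mediation analyses. If results are shown by delivery mode, give the caesarean rate in each arm beside them, since that grouping is itself formed after randomisation.

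The cost is a change of wording in the protocol and the analysis plan. The sample size of 780 and the stated 80% power are unaffected. The listed variables are already due to be collected; the one point to confirm is that attitude and intention are recorded at enrolment.

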### 3.6. Ethical Issues

The study protocol has been approved by the Curtin Human Research Ethics Committee (Ref: HRE2019-0143) and the Ethical Review Board for Biomedical Research, Hanoi University of Public Health (Ref: 28/2019/YTCC-HD3). 

Potential participants will be invited to take part in this ‘maternal and child health’ study. After briefing them about the purpose and research procedure, they will be asked to sign the written consent form in Vietnamese. Participants are free to withdraw at any time or may decline to answer any question at the baseline and follow up surveys without prejudice. Any problem or difficulties will be referred to health professionals. All participants and their infants, irrespective of their group allocation, will receive standard health services and hospital care. There are no potential risks for the participants involved in the study. All participants will be de-identified before data collection. Survey data captured through REDCap will be password protected and stored at the Curtin secure server, and accessible by the Curtin project manager and Chief Investigators only. Findings will be presented in an aggregate format in subsequent publications.

## 4. Discussion

Breastfeeding rates, particularly exclusive breastfeeding, are declining in Vietnam and almost all the rapidly developing countries in the Asia Pacific region. If breastfeeding rates can be improved there will be many benefits to short and long term health outcomes [133]. It is important to reverse this trend and increase the rates in order to improve the health of the population, and to assist in achieving the United Nations (UN) Sustainable Development Goals and improving the environment [134]. The costs of not breastfeeding are a significant drain on health services and the national economy [135,136].

The proportion of mothers in Vietnam who have access to a smartphone has now reached above 90%. There are 145 million active mobile phone connections for a population of 97 million [137]. We hope to achieve our outcomes given mobile apps increasingly being applied to improve maternal and infant health [138]. We anticipate that the widespread use of smartphone will offer great potential for implementing interventions to promote exclusive breastfeeding in Vietnam.

### Strengths and Limitations

This trial hypothesizes that there will be higher rates and longer duration of exclusive breastfeeding for up to 6 months after childbirth in the intervention group compared with its control counterpart. The study, to our knowledge, will be the first mobile app-based intervention to support breastfeeding in Vietnam. A blinded randomised control trial that can provide the most rigorous evidence of intervention effectiveness. The intervention content will be developed by experts in the field, and an app will be designed for two common mobile operating systems (iOS and Android). Data collection and management will be undertaken in a secured environment through REDcap so that data quality and protection can be ensured. The study will fill an important gap by developing a novel mHealth intervention addressing suboptimal breastfeeding in LMICs.

However, the study has some limitations. The intervention and control group may differ in terms of socio-demographic characteristics, potentially limiting comparison between the two groups on breastfeeding outcomes. Nonetheless, a statistical analysis plan will be developed, including adjustment for baseline covariates [139,140,141]. In fact, the CONSORT statement recommended against performing significance testing of baseline differences in randomised controlled trials [142]. Moreover, a stratified permuted-block randomisation will be undertaken with consideration of three key factors (i.e., maternal age, education and parity) associated with breastfeeding behaviours, perception and practices. Loss to follow-up is also a matter of concern because it may bias the results [143], particularly if missing data is associated with breastfeeding. To cope with this potential problem, we will adopt different strategies to maintain a high level of participant retention such as building positive rapport between participants and the study team, sending reminders, providing incentives, etc. [144,145,146]. In addition, appropriate methods will be applied to handle missing data, including inverse probability weighting, likelihood-based methods, and multiple imputation [147,148]. Another possibility is no or low usage of the mobile app under the study, but we will send reminders to encourage participants and conduct intention-to-treat analysis accordingly.

## 5. Conclusions

Breastfeeding has many advantages for mothers and infants in the short term and for lifetime health. The coverage in Vietnam of mobile phones is now above 90% making it eminently feasible to use smart phones for promoting breastfeeding. The app will be developed to promote early initiation of breastfeeding and exclusive breastfeeding for the first six months of life. In particular, the app will seek to overcome the low rate of breastfeeding following caesarean section. 

## Figures and Tables

**Figure 1 ijerph-17-05552-f001:**
[figure not shown]
Study design and interventions.
